#### Missing data

We will review survey completeness and recontact respondents to address quality issues and increase response rates. Logistic regression will be used to determine the type of missingness. Within waves, multiple imputation techniques will be applied. To address issues of missing data across different waves (i.e., over time), we will use generalized estimating equations (GEE) or weighted GEE, depending on the type of missing data.

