### Power analyses

The expected sample (475 paired counties, up to 4 respondents per county, resulting sample size of ~ 3800) and the response rate of 50% gives an expected sample of 1900 respondents. Given that anywhere from 0 to 4 respondents may complete the survey in any given county, with a 50% overall response rate, we anticipate that 712 counties will have at least one respondent who completes the survey. We used a conservative (higher than expected) intraclass correlation coefficient of 0.1 for addressing clustering of agencies within counties.

For county-level analysis, an effect size of 0.2, power of 0.8, confidence level of 95%, and statistical significance level of 0.05 were used to calculate the minimum sample size. Repeated measures analysis required a minimum total sample size of 304 counties. For logistic regression and other nonlinear predictive models, depending on the type and quantity of variables used in the model, the minimum total sample size required varied between 156 and 489 counties. With attrition, our calculations showed a power of 0.9 and more for most county-level analyses.

For agency-level analysis, a conservative agency-level effect size estimate (*d* = 0.1), a power of 0.8, confidence level of 95%, and significance level of 0.05 were used to calculate the minimum required sample size. Repeated measures analysis comparing respondents from Stepping Up and comparison counties resulted in a minimum sample size of 524 respondents. When comparing the response measures, measured at the agency level, over time, a minimum sample size of 1200 respondents is required. For predictive logistic regression and other nonlinear predictive models, the minimum sample size varied between 673 and 1100 respondents. Given the larger sample size of this study, our calculations showed a power higher than 0.9 for agency-level analyses.

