### Analysis plan

#### General approaches

Primary tests will be 2-sided with α = 0.05. Analysis approaches accommodate nested and repeated measures data. We will examine predictive associations between Stepping Up membership, hypothesized target mechanisms, and implementation outcomes over time. We will use general linear models and generalized linear mixed models (GLMM) when the dependent variables are continuous and noncontinuous, respectively. GEE will be used instead when distributional assumptions are not met. For non-aggregated dependent variables reported at the agency level (i.e., hierarchical data), a random intercept growth hierarchical linear model (GHLM) will be fitted. All analyses will covary: (1) Wave 1 (baseline) values of dependent variables, (2) months since the county joined Stepping Up, (3) the matching score, (4) an indicator representing whether a the county shares their mental health administrator with other counties, and (5) a similar indicator for shared justice roles across counties.

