#### Aim 1a: comparison of target mechanisms between Stepping Up and non-Stepping Up counties

##### Primary

We will test the hypothesis that Stepping Up counties will show faster rate of improvement in *the use of/ capacity for performance monitoring* (i.e., total scores on our Performance Monitoring measure) than comparison counties, using GLMM or GEE. Analyses will test for differences in slopes (rates of change). Separate secondary analysis will compare rates of change in the adapted Routine Decision-Making scale total score between Stepping Up and comparison counties.

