#### Aim 2: comparison of implementation outcomes between Stepping Up and non-Stepping Up counties

##### Primary

We will test the hypothesis that Stepping Up counties will show faster rate of improvement in the number of justice-involved clients receiving behavioral health services than will comparison counties, using GLMM and GEE. Analyses will test for differences in slopes (rates of change) between the two sets of counties.

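### A logistic regression cannot determine the missing-data type, so it should not decide whether the across-wave GEE is weighted

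*Protocol article*

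**What the plan says.** The Missing data section of the protocol article sets out three steps.

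- Diagnosis: "Logistic regression will be used to determine the type of missingness".
- Gaps within a wave: "Within waves, multiple imputation techniques will be applied".
- Gaps across waves: "we will use generalized estimating equations (GEE) or weighted GEE, depending on the type of missing data".

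It names no other method for across-wave gaps and no analysis under MNAR.

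GEE is one of the methods for both primary slope comparisons. Aim 1a (performance monitoring) is analysed "using GLMM or GEE. Analyses will test for differences in slopes (rates of change"), and Aim 2 (clients receiving services) compares Stepping Up counties' improvement as faster "than will comparison counties, using GLMM and GEE". For system integration, under Aim 1a secondary analyses, GEE is the only method named. General approaches adds a separate trigger: "GEE will be used instead when distributional assumptions are not met". The same section fixes the adjustment: "All analyses will covary: (1) Wave 1 (baseline) values of dependent variables", followed by months since joining, the matching score and two shared-administrator indicators.

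**The concern.** The rule asks the regression for something it cannot supply. A logistic model of response uses observed values only. A clear association is evidence against MCAR. No association does not establish MCAR, and neither result says whether missingness also depends on the unseen value, which is what separates MAR from MNAR.

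The answer nevertheless selects the estimator. If no dependence is found, the natural choice is unweighted GEE, which needs missingness to be MCAR or to depend only on covariates in the model. When real dependence on an earlier outcome goes undetected, the difference in slopes, which is the quantity tested in Aims 1a and 2, can be biased and its type I error inflated. If missingness is MNAR, neither branch protects.

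**Working it through.** **Inputs from the article.** Three waves (baseline, 18 and 36 months); two-sided α = 0.05; Wave 1 value covaried; county-level planning effect 0.2; 712 counties with at least one respondent. Power analyses also says "the response rate of 50% gives an expected sample of 1900 respondents": 3800 × 0.50 = 1900, which reproduces. That 50% is overall survey response. The same section allows for attrition but gives no rate for it.

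**Assumed, because the article gives no figure.** Correlation between waves, amount of dropout, and its strength and direction. The true slope difference is set to 0 throughout, so any average estimate is bias.

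**Model.** Dropout: logit P(drop) = a + b·s·x, where x is the outcome driving dropout, b the log-odds per outcome SD, and s gives the direction in each group. Analysis of Waves 2 and 3, t = 0, 1: E(Y) = β0 + β1·G + β2·t + β3·G·t + β4·Y(Wave 1), testing β3 with robust standard errors and independence working correlation. Weights are the inverse of the fitted probability of still being observed.

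**Check 1: can the regression tell the types apart?** 1900 independent respondents, correlation 0.5, opposite directions in the two groups, 300 replicates. With a = −0.85 the dropout probability is about 0.30 per step, so about 0.70 × 0.70 = 0.49 remain at Wave 3. The logistic test includes group interactions.

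| Dropout depends on | b | Test flags | Unweighted: bias, type I | Weighted: bias, type I |
|---|---|---|---|---|
| nothing (MCAR) | 0 | 6% | −0.004, 4.0% | −0.004, 4.0% |
| Wave 1 (MAR) | 0.5 | 100% | 0.005, 5.0% | 0.007, 5.3% |
| Wave 2 (MAR) | 0.5 | 100% | 0.072, 20.3% | 0.001, 4.3% |
| Wave 2 (MAR) | 0.15 | 46% | 0.023, 7.7% | −0.001, 3.7% |
| Wave 3 value (MNAR) | 0.5 | 96% | 0.220, 93.7% | 0.197, 88.7% |
| unseen change (MNAR) | 0.5 | 3% | 0.053, 13.3% | 0.053, 13.3% |
| unseen change (MNAR) | 0.3 | 6% | 0.029, 9.7% | 0.029, 6.3% |

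The Monte Carlo error of a 5% rate is √(0.05 × 0.95 / 300) = 1.3 percentage points.

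- One MNAR mechanism is flagged as rarely as MCAR (3 to 6% against 6%). Another is flagged almost as often as MAR (96% against 100%). The test result does not identify the type.
- Dropout driven by Wave 1 alone leaves adjusted, unweighted GEE at its nominal level.
- Weak Wave 2 dependence is missed in 100 − 46 = 54% of replicates.

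**Check 2: size at county level.** 712 counties, correlation 0.6, about 25% missing at Wave 3, Wave 1 covaried unless stated, 600 replicates per scenario.

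| Dropout depends on | b | Unweighted bias (SD) | Logistic test |
|---|---|---|---|
| Wave 1, one group, covariate omitted | 0.3, 0.4 | 0.049, 0.063 | – |
| Wave 1, one group, covariate included | 0.3, 0.4 | 0.002, 0.005 | – |
| Wave 2, opposite directions | 0.3–0.5 | 0.04–0.08; type I 7–17% | main effects flag 5–6%; with interactions 77–100% |
| Wave 2, one group only | 0.3–0.5 | 0.02–0.03 | main effects miss 29–69% |
| unseen change (MNAR) | 0.3–0.5 | 0.03–0.13 | main effects flag 4–25% |

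A second set of runs of the Wave 2 case gave bias of 0.01 to 0.06 SD and type I error up to 11%. The main-effects test missed the dependence 28 to 96% of the time, and weighted GEE was unbiased.

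Against the planning effect, read in SD units: 0.01/0.2 = 5%, 0.06/0.2 = 30%, 0.08/0.2 = 40%.

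**The case against.** **Mixed models are planned.** General approaches plans mixed models for noncontinuous and agency-level outcomes, and both primary analyses name GLMM. A correctly specified likelihood-based mixed model is valid under MAR. This stands in part: not every result rests on unweighted GEE. But the Missing data section names only GEE or weighted GEE for gaps across waves, and the primary analyses do not say which of GLMM and GEE governs.

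**The rule is loosely worded.** The article gives no significance threshold and does not say which type leads to which GEE. That is so, and pairing unweighted GEE with apparent MCAR is an inference, though the natural one. Logistic modelling of response is also the usual way to build weights. Detail of that kind belongs in an analysis plan, but no further detail would let this regression determine the type.

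**A good test would catch the worst cases.** With group interactions, the strongest Wave 2 dependence is flagged in up to 100% of replicates and weighted GEE would follow. This stands for strong dependence. It does not cover weak dependence, and the article does not say that interactions are included.

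**MNAR is nobody's special fault.** No method fitted to observed data resolves it, MAR-valid methods included, and a protocol article may leave a sensitivity analysis to the analysis plan. Agreed; its absence is not counted as an error here.

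**Two stronger readings are tempting.** A reader might infer that unweighted GEE is valid only under MCAR, so that dropout related to baseline would bias the slopes by about 0.05 to 0.06 SD. The documents do not support this: Wave 1 is covaried in all analyses, and with it the bias was 0.014 SD or less in every run. A reader might also take the 50% as loss between waves. It is overall survey response and includes people who may never respond, whom weights based on earlier waves cannot reach.

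**Conclusion.** The point holds in a limited form. The stated diagnostic cannot determine the missing-data type and should not select the estimator. That conclusion is a matter of logic and does not depend on the simulations.

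The practical harm is modest and conditional. It needs GEE to be used, the pretest to miss the dependence, and dropout to depend on Wave 2 beyond Wave 1 and differently in the two groups. Under the assumed county-level settings this gives a bias of about 0.01 to 0.06 SD, up to 0.08 SD in the less favourable runs, with type I error of about 5 to 17%. The correlation, the 25% missing and the dropout strengths are assumptions, so the range is illustrative. It also assumes an independence working correlation, which the article does not specify.

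**What to change.** Drop the pretest. State that across-wave missingness in the primary slopes is always handled by a MAR-valid method, whatever the logistic regression shows:

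- the already planned likelihood-based mixed model (GLMM or GHLM) on all available waves; or
- where GEE is needed, always-weighted GEE, with prior-wave outcome, group, their interaction and agency type in the weight model. The interaction matters: if dependence runs in opposite directions in the two groups, main effects cancel and the weights correct nothing.

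Use the logistic model only to build the weights. Optionally, add one delta-adjusted sensitivity analysis for the primary outcomes, since neither form of GEE protects against MNAR.

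The cost is a change of wording, modest extra analysis, and slightly wider intervals if the data are in fact MCAR. No new data are needed.

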## Implementation mechanisms of Stepping Up (I.M. Stepping Up) study aims

This study will compare Stepping Up counties to matched comparison counties on implementation outcomes and mechanisms (see Table 1). We will use surveys and qualitative interviews to compare 475 Stepping Up and 475 paired target counties at 3 waves: study baseline, 18 months, and 36 months (see Fig. 2). County- and agency-level data will be collected from individuals in 4 specific criminal justice and behavioral health administrator roles in each county (up to 3800 total respondents at each wave). Stepping Up and comparison counties will be compared on rates of change in engagement of target mechanisms (primary) and rates of change in implementation outcomes (secondary). Specific aims are to
*Compare engagement of target implementation mechanisms between Stepping Up and comparison counties.* We will examine whether (a) Stepping Up counties show a faster rate of improvement in hypothesized target mechanisms (use of/capacity for performance monitoring, use and functioning of interagency teams, common goals across agencies, and system integration) than do comparison counties; and (b) whether target mechanisms mediate effects of Stepping Up on implementation outcomes.*Compare implementation outcomes between Stepping Up and comparison counties.* We will examine whether Stepping Up counties show faster rate of improvement in implementation outcomes (number of justice-involved clients receiving behavioral health services, number of behavioral health EBPP available to justice-involved individuals, and resources for behavioral health EBPP for justice-involved individuals) than do comparison counties.*Characterize implementation processes and critical incidents* occurring in Stepping Up and comparison counties. We will (a) use qualitative data to triangulate quantitative findings and enrich an understanding of how the target mechanisms produce outcomes, (b) assess counties’ fidelity to Stepping Up, and (c) explore which naturally occurring implementation strategies used in 950 counties lead to better implementation outcomes.

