### Measures

Measures will be collected at all 3 time points (see Table 3). All respondents will receive the same assessments. We refer to measures as “agency-level measures” when analyses of these measures will account for nesting within counties, but the primary focus is on agencies. We refer to measures as “agencies nested within counties” when we used nested analyses and our primary focus is on the county level. We refer to measures as “county-level” measures if they produce a single value for the county to be analyzed at the county level.

**Table 3 Tab3:** Study assessments

Construct	Measures and indicators	Time point		
		Baseline	8 months	36 months

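### For agency-reported outcomes the plan requires a Wave 1 covariate but imputes only within waves, so agencies that first answer at 18 or 36 months have no sound route into the models

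*Protocol article*

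**What the plan says.** All statements are in the protocol article.

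- Study aims: four administrator roles per county are surveyed, with "up to 3800 total respondents at each wave". The Measures section adds: "Measures will be collected at all 3 time points".
- Power analyses: "the response rate of 50% gives an expected sample of 1900 respondents".
- Analysis plan, General approaches: "All analyses will covary: (1) Wave 1 (baseline) values of dependent variables". The Methods introduction, Table 3 and the Discussion repeat this adjustment.
- Missing data: "Within waves, multiple imputation techniques will be applied". For missingness over time the section names GEE, or weighted GEE, according to the type of missingness.
- Both primary measures are reported by agencies nested within counties: the Performance Monitoring score (Aim 1a) and the number of justice-involved clients receiving services (Aim 2). Both hypotheses concern rates of change.

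**The concern.** Each rule is ordinary alone; together they leave a gap. With half the targeted agencies not answering at a given wave, some will miss Wave 1 and answer later. Such an agency has follow-up outcomes but lacks a covariate that all models require. GEE uses records whose covariates are observed. Weighted GEE reweights for outcomes that are missing and does not create a baseline. Imputation confined to a wave cannot use the agency's own 18- and 36-month answers, which are likely to be among the best predictors of its Wave 1 value.

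At stake is follow-up data that the study pays to collect. An agency that answers at both 18 and 36 months has an observed change yet may not count in the test of change. The comparison is then about agencies that responded at Wave 1. If Wave 1 response differed between Stepping Up and comparison counties, the contrast could be biased as well as less precise.

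**Working it through.** **Inputs from the protocol article.** 950 counties with four roles each give 3800 targets per wave. Response is 50%. There are three waves. The power section uses an "intraclass correlation coefficient of 0.1 for addressing clustering of agencies within counties" and, at d = 0.1, a "conservative agency-level effect size estimate". Tests are two-sided at 0.05.

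**Assumptions of this check.** The 50% applies at each wave. Response is exchangeable across waves (beta-binomial) with pairwise correlation r. The document does not give r, so it is varied from 0 (independent waves) to 1 (the same agencies always answer).

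**Step 1: the plan's figure.** 3800 × 0.50 = 1900 respondents, as stated. The other 1900 have no Wave 1 value.

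**Step 2: late responders.** With 50% response:

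- P(miss Wave 1, answer Wave 2) = (1 − r)/4, and the same for Wave 3.
- P(miss Wave 1, answer both later waves) = (1 − r)/8, so the count is 475(1 − r).
- P(miss Wave 1, answer at least one later wave) = 2(1 − r)/4 − (1 − r)/8 = 3(1 − r)/8, so the count is 1425(1 − r).
- Agencies with Wave 1 and at least one later wave number 1900 − 475(1 − r).

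| r | No Wave 1, both later waves | No Wave 1, at least one later wave | Wave 1 and at least one later wave | Share of agencies with follow-up lacking Wave 1 |
|---|---|---|---|---|
| 0 | 475 | 1425 | 1425 | 50% |
| 0.25 | 356 | 1069 | 1544 | 41% |
| 0.5 | 238 | 712 | 1662 | 30% |
| 0.75 | 119 | 356 | 1781 | 17% |
| 0.9 | 48 | 143 | 1852 | 7% |
| 1 | 0 | 0 | 1900 | 0% |

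Counts are rounded to whole agencies. The 712 and 238 agencies at r = 0.5 match the power section's 712 counties, and 950 − 712 = 238, only by coincidence.

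**Step 3: precision.** Take a simple two-group comparison with n agencies, m = n/950 per county and design effect DE = 1 + (m − 1) × 0.1. Then power = Φ(d√(n/(4·DE)) − 1.96). At r = 0.5 and d = 0.1:

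- Wave 1 required: n = 1662.5, m = 1.75, DE = 1.075, and Φ(1.966 − 1.96) = 0.50.
- Late responders retained: n = 2375, m = 2.5, DE = 1.15, and Φ(2.272 − 1.96) = 0.62.

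The same contrast at d = 0.1 is 0.45 against 0.68 at r = 0, and 0.54 against 0.56 at r = 0.9. At d = 0.2 it is 0.96 against 1.00 at r = 0, and 0.98 against 1.00 at r = 0.5. The retained figures treat an imputed baseline as if it were observed, so they are upper bounds on the gain.

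**Step 4: county-level outcomes.** The EBPP count, within-county agreement and shared-instrument score take the county's Wave 1 value. A late agency still contributes if enough other agencies in its county answered at Wave 1: one for the EBPP count, at least two for the other measures.

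**The case against.** The strongest reply is that this is a condensed article and that handling of a missing baseline belongs in an analysis plan that is not shown. Nothing in the text excludes late entrants. Within-wave imputation is not expressly limited to item non-response, so it could fill a whole Wave 1 record from other agencies in the county, the matching score and county covariates. The growth model is not described closely enough to show how Wave 1 enters it. Re-approaching Wave 1 non-responders is implied by the per-wave target, not stated for the survey. The plan also works to limit non-response through reminders, phone calls, a paper option, a six-month window and recontact.

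Much of this stands. It means that loss is the result of a standard fit, not a declared exclusion. It does not remove the point, because the article does more than stay silent: it states the covariate rule, the imputation scope and the cross-wave method. Followed as written, the best available outcome is a baseline imputed without the agency's later answers.

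A reader might infer three stronger things that the article does not support:

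- **That every model is affected.** This is wrong for the county-level outcomes in Step 4.
- **That 950 − 712 = 238 counties have no Wave 1 value.** The power section says "we anticipate that 712 counties will have at least one respondent who completes the survey" but does not tie this to Wave 1. A county that never responds also loses nothing through the covariate rule.
- **That the arms were recruited by different means, so bias follows.** The contact list came only from the Stepping Up side, but Survey respondents describes web searching in both arms. A difference in Wave 1 response is a possibility only.

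**Conclusion.** The point holds for agency-reported outcomes, including both primary ones. The stated combination of rules either drops agencies that first answer after Wave 1 or imputes their baseline inefficiently. Under 50% response at each wave and exchangeable response, this concerns 1425(1 − r) agencies with some follow-up, of whom 475(1 − r) answered both later waves. That is half of all agencies with follow-up at r = 0, 30% at r = 0.5, 7% at r = 0.9 and none at r = 1. The article does not give r, so the range is the result and no single value should be quoted.

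Power is not the main harm. The restriction alone does not take power below 0.9 at d = 0.2, and at d = 0.1 the simple comparison is below 0.9 with or without it. The main harm is that the primary comparisons are confined to Wave 1 responders when a better method is available from the same data. The number of counties affected on county-level outcomes cannot be read from the document.

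**What to change.** In Missing data, replace within-wave imputation with multiple imputation done jointly across the three waves, with group, agency type, county and the other planned covariates in the imputation model. State that it covers agencies with no Wave 1 survey. Keep the Wave 1 covariate in the primary models: the groups are self-selected and the plan uses that covariate for confounding control, so dropping it could change the contrast being estimated. A longitudinal model with Wave 1 as the first repeated outcome, and group, time and group-by-time terms, can serve as a sensitivity analysis.

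The cost is a change of wording and modest programming, with no new data. The price is a missing-at-random assumption for Wave 1 non-response, which should be stated.
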